### Types of interventions

After inclusion, patients will be randomly assigned to either one of three groups illustrated in Figure 1: (1) IHT plus fluoxetine dummy-loaded; (2) fluoxetine (20 mg/day) plus IHT dummy-loaded; and (3) fluoxetine placebo plus IHT placebo.

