### Criteria for discontinuing or modifying allocated interventions

Some adverse effects have been observed during fluoxetine treatment: lack of interest in sex, sexual dysfunction, nausea, insomnia, somnolence, anorexia, anxiety, asthenia, tremor, allergic skin reactions. If they are serious and/or result in interruption of treatment, they will be reported as adverse events.

During the IHT participants could have one of these reactions: (1) temporary intensification of symptoms before the condition improves, which is named ‘homeopathic aggravation.’ If it occurs at all it is usually mild and simply an indication that the body is resolving the problem in a natural and healthy way. If aggravation is too distressing it will be lessened by using frequent doses of the same remedy in a lower potency; (2) improving symptoms without aggravation; and (3) the appearance of new symptoms different from those on which the prescription was based. They will be reported as adverse events. They are rarely serious, but in that case, the IHT will be stopped. If the participant experiences the same symptoms of the remedy, the corresponding antidote will be prescribed.

Each participant will receive a report form on which to write daily any adverse event observed during the trial duration. Study participants will be retained in the trial whenever possible to enable follow-up data collection and prevent missing data.

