### Concomitant interventions

Some medications are prohibited during the study duration: triptans, tramadol, anxiolytic drugs, other serotonergic agents or antidepressants, as well as hormone replacement therapy. Psychotherapy is also forbidden during the study duration. Medication for diabetes and hypertension is allowed. The rescue intervention in case of a lack of efficacy in the IHT and placebo groups will be fluoxetine 20 mg/day; in the fluoxetine group, the rescue medication will be sertraline 25 mg/day.

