### Outcomes

The primary efficacy outcome is the change from baseline in mean total depression score using the 17-item version of the HRSD at weeks four and six. The severity of symptoms will be assessed by a blinded investigator (clinical psychologist) from the JMH. The secondary outcomes are: change from baseline in mean total depression score using BDI (a self-reported scale) at weeks four and six; change from baseline in mean total score of GS at weeks four and six; responder rates (response rate: decrease of 50% or more from baseline score; remission rate: HRSD ≤7). The number and severity of all adverse events and homeopathic aggravations during the study period and 15 days after the final dose will be collected to determine the safety of fluoxetine and homeopathic medicines. An adverse event will be defined as any untoward medical occurrence in a subject without regard to the possibility of a causal relationship. Adverse events will be collected after participants have given consent and enrolled in the study and 15 days after study completion.

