### Statistical analysis

All patients under randomization will be included in the primary efficacy population (intention-to-treat population), regardless whether or not they adhered to the treatment protocol or provided complete data sets. Only patients who withdraw their consent to use their personal data will be excluded from the analysis. The flow of participants through the trial will be presented in a Consolidate Standards of Reporting Trials (CONSORT) diagram.

First, the three groups will be compared in order to verify that there are no significant differences among them at baseline to confirm they are comparable after randomization. Demographic characteristics will be summarized using means and standard deviation for continuous data (that is, age) and relative frequencies for qualitative data (that is, marital status, comorbidities). The baseline demographic characteristics among groups will be compared with the use of the chi square test or by one-way independent measures of analysis of variance (ANOVA) as required.

We will compare: (1) IHT versus placebo; (2) fluoxetine versus placebo; and (3) IHT versus fluoxetine. The main statistical analysis will compare primary and secondary outcome measurements among groups at weeks four and six. The primary outcome (change in mean HRSD score) and secondary outcomes (change in mean BDI and GS scores) among groups at baseline and weeks four and six, will be analyzed by one-way ANOVA to provide a statistical test of whether or not the means of the three groups are all equal. The statistically significant one-way ANOVA result (*P* <0.05) suggests rejecting the global null hypothesis H_0_ (that the means are the same across IHT, fluoxetine and placebo groups). The Bonferroni *post-hoc* test will be used to determine which means differ among the groups. Responder rates will be compared among the groups using the chi square test. Statistical significance will be set at *P* <0.05 level for all analysis. Missing data will be handled by sensitivity analysis.

All patients who received at least one dose of the study drugs will be considered in the safety analysis. Adverse events will be translated to Medical Dictionary for Regulatory Activities terms (MeDRa terms), quantified and compared among the groups using the chi square test. Homeopathic aggravation will be compared among the groups also using the chi square test.

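### Adverse events that begin after rescue are not separated in the safety comparison, although rescue in two arms is the comparator drug, so the result depends on how many women are rescued in each arm

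*Protocol article*

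**What the plan says.** Four parts of the protocol article bear on this.

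- **Treatments.** Under Types of interventions, the active comparator arm is "fluoxetine (20 mg/day) plus IHT dummy-loaded".
- **Rescue.** Under Concomitant interventions: "The rescue intervention in case of a lack of efficacy in the IHT and placebo groups will be fluoxetine 20 mg/day"; and "in the fluoxetine group, the rescue medication will be sertraline 25 mg/day".
- **Event collection.** Under Outcomes, adverse events of every kind, together with aggravations on the remedy, are counted and graded; the window and purpose read "during the study period and 15 days after the final dose will be collected to determine the safety of fluoxetine and homeopathic medicines". The same section defines an adverse event without reference to cause. Under Criteria for discontinuing or modifying allocated interventions, each woman receives "a report form on which to write daily any adverse event observed during the trial duration", and women are to be kept in follow-up where possible.
- **Analysis.** Under Statistical analysis: "All patients who received at least one dose of the study drugs will be considered in the safety analysis". Adverse events are then coded, "quantified and compared among the groups using the chi square test". In that section the groups named are IHT, fluoxetine and placebo. No as-treated grouping is defined, and nothing there refers to rescue.

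**The concern.** Safety is a named secondary aim, and event collection is meant to establish the safety of fluoxetine and of the homeopathic medicines. After rescue, a woman randomised to placebo or IHT may be taking the drug against which her arm is compared. Nausea or insomnia, both on the article's own list of fluoxetine effects, would then be tallied under placebo or IHT. An event on sertraline would be tallied under fluoxetine. Because the definition of an adverse event ignores cause, causality does not filter these events out either.

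Analysing the depression scores as randomised whatever the rescue is a separate, defensible choice. Here the question is what a drug does to the women who take it, and a count that mixes in another drug's events does not answer that cleanly.

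**Working it through.** The plan has no figure to reproduce: it gives no event rate, rescue rate or safety power. The calculations show direction and plausible size only.

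**Inputs from the article:** 63 women per group; two-sided 5% level; visits at weeks four and six; collection to 15 days after the final dose, taken here as 42 + 15 = 57 days.

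**Assumed inputs:** event risk p0 without an antidepressant and p1 on fluoxetine; rescued fractions r (placebo or IHT) and s (fluoxetine); rescued placebo or IHT women reach risk p1; sertraline adds the same excess among fluoxetine women who are still event-free.

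**Formulas**

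- Placebo or IHT arm: p0 + r(p1 − p0)
- Fluoxetine arm: p1 + s(1 − p1)(p1 − p0)/(1 − p0)

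**Step 1. Fluoxetine against placebo, with p0 = 15% and p1 = 35% (true difference 20 points).** Power is for a pairwise test of two proportions with 63 per arm.

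| Placebo rescued | Fluoxetine rescued | Placebo arm | Fluoxetine arm | Difference (points) | Power |
|---|---|---|---|---|---|
| 0% | 0% | 15% | 35% | 20 | 74% |
| 10% | 0% | 17% | 35% | 18 | 64% |
| 20% | 0% | 19% | 35% | 16 | 53% |
| 30% | 0% | 21% | 35% | 14 | 42% |
| 20% | 20% | 19% | 38.1% | 19.1 | 66% |
| 10% | 20% | 17% | 38.1% | 21.1 | 76% |

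The 38.1% is 35 + 0.2 × 65 × (20/85). The first four rows show dilution. The last two show it almost cancelling and then reversing. With p0 = 25% and p1 = 50% the pattern is the same: 25 points become 20 with 20% rescue in placebo only, and 23.3 with 20% in both arms.

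**Step 2. IHT against placebo, both with a true risk of 15%.** With 10% rescued in IHT and 30% in placebo, IHT shows 15 + 0.1 × 20 = 17% and placebo 15 + 0.3 × 20 = 21%. Rescue alone creates a 4-point gap.

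**Step 3. Would cutting at rescue and comparing proportions cure it?** Take risks over 57 days of 30% (placebo) and 50% (fluoxetine), constant rates, rescue at week four (28 days before, 29 after) in 30% of placebo women, and none in fluoxetine.

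- All events counted: the daily rates are −ln(0.7)/57 = 0.00626 and −ln(0.5)/57 = 0.01216. A rescued woman's risk is 1 − exp(−(28 × 0.00626 + 29 × 0.01216)) = 41%. The placebo arm shows 0.7 × 30 + 0.3 × 41 = 33.3%, so the difference is 16.7 points, an error of −3.3.
- Pre-rescue events as proportions: a rescued woman's risk over 28 days is 1 − 0.7^(28/57) = 16.1%. The placebo arm shows 0.7 × 30 + 0.3 × 16.1 = 25.8%, so the difference is 24.2 points, an error of +4.2.
- Pre-rescue events per woman-day at risk: under constant rates the placebo arm returns 0.00626 per day whatever fraction is rescued, because the shorter window enters the denominator as well.

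A bare proportion of pre-rescue events therefore trades one error for another of similar size. The rate does not, provided that the rate is roughly constant and rescue is unrelated to event risk.

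**The case against.** The strongest objection is that no sentence assigns events after rescue to the randomised arm. The safety-population sentence says only who is included, and the comparison is among groups not labelled as randomised or as treated. This is a condensed article, and attribution windows often sit in a full protocol or analysis plan that is not shown. That stands in part: attribution by arm is an inference. But the article does fix the rescue drugs, the event window, the cause-free definition, the three groups and the test. Followed together, those rules mix rescue-drug events into the arm counts, which is more than missing detail.

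A reader might also infer that the safety comparison is simply pulled towards no difference. The documents do not support that. Sertraline rescue in the fluoxetine arm can offset or reverse the dilution, and unequal rescue can create an IHT-placebo gap.

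Three further points stand. An all-events comparison as randomised is a recognised safety table and should not be discarded. Every rate used here is assumed: rescue at week six would leave 15 of the 57 days after rescue, not 29, and some rescued women may not stay in follow-up. Finally, the article sizes the trial for the HRSD only and claims no power for safety, so the power figures merely illustrate.

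**Conclusion.** The concern holds in limited form. The stated rules do not separate events that begin after rescue, and on the natural reading by randomised arm the safety comparison partly reflects differential rescue. Fluoxetine's difference from placebo or IHT is diluted when rescue is mainly in the placebo and IHT arms. In other patterns the direction depends on the rescue rate in each arm. The documents establish neither a fixed direction nor a size. Under the 15% and 35% illustration, a true 20 points is seen as anything from 14 to 21.1 points across the rescue patterns tabulated. This affects a secondary aim, leaves the HRSD analysis untouched, and is worth correcting because the correction is nearly free.

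**What to change.** In Statistical analysis, add to the safety paragraph:

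1. Classify each adverse event by onset before, or on or after, the first rescue dose, using the daily report forms.
2. Compare pre-rescue events among the three groups as rates per woman-day at risk, not as bare proportions, which understate risk in arms with more rescue.
3. List events after rescue separately, by the antidepressant actually taken.
4. Keep the all-events table by randomised arm alongside, and show the number rescued in each arm.

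The cost is analysis wording; the daily forms are already planned, and the date of first rescue must be recorded. The downside is small: pre-rescue follow-up is shorter for rescued women, and a cut at rescue for lack of efficacy may be informative, which is why both tables are shown. No rescue rule changes.

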### Auditing

The Research and Ethics Committee of JMH, which is not involved in the study, will review the trial process every three months.

### Confidentiality

All study-related information will be stored securely at the study site. Participants’ study information will not be released outside of the study without the written permission of the participant.

### Regulatory and ethical approval

The trial protocol has been reviewed and approved by the Research and Ethics Committee of the Juárez de México Hospital (Submission Nº HJM 2030/12-A). This study is in compliance with the Helsinki Declaration and with the International Conference on Harmonisation (ICH) – Good Clinical Practice. Prior to undertaking any study related procedures, each participant will receive a verbal and written explanation of study aims, methods, potential hazards, and benefits from investigators and will provide written informed consent.

### Post-trial care

In the case of adverse events and after the completion of the study, participants may continue receiving health care at JMH.

## Discussion

For the first time this study evaluates both the specific effect of IHT using C-potencies versus fluoxetine and placebo in peri- and postmenopausal women with moderate to severe depression. Besides comparing homeopathic medicines versus placebo, the fluoxetine-arm will give more useful information about the effect of IHT versus an efficacious treatment for depression in a randomized controlled trial. It is an attempt to deal with the obstacles of homeopathic research due to the need of individual prescriptions in one of the most common psychiatric disorders. Homeopathy is frequently prescribed for climacteric symptoms including depression as it has been proven in some observational studies, but there is a lack of high-quality trials to prove its efficacy. This study protocol is based on: (1) CONSORT guidelines for reporting randomized trials with parallel groups; (2) the reporting data on homeopathic treatments (RedHot) supplement to CONSORT [32,33]; and (3) the Standard Protocol Items: Recommendations for Interventional Trials (SPIRIT) 2013 guidance for protocols of clinical trials [34].

It has been reported that the homeopathic consultation is in itself a therapeutic intervention working independently of the prescribed remedy [35], so all study participants will go through the same full homeopathic case-taking regardless of group allocation. Because placebo interventions are associated with mean response or remission rates of 35% [36,37], this trial includes a placebo-arm, so placebo effect can be ruled out.

Gibbons *et al.* reported that patients in all age and antidepressant groups have significantly greater improvement relative to placebo controls; and fluoxetine has been proven to be efficacious for depression in adults after six weeks of treatment [38], so it is expected that the fluoxetine-arm will result in significant differences versus placebo in this study. However, Kirsch *et al.* reported that, at present, it is becoming more difficult to prove that antidepressants actually work better than placebo in moderate to severe depression. It also has to be taken into consideration that the antidepressant-placebo difference seems to be smaller in the trials with moderately depressed participants [13]. Therefore, a fluoxetine-arm will allow us to detect if in Mexican women in the climacteric stage with moderate to severe depression, the difference in HRSD score between fluoxetine and placebo is as small as it has been shown in some meta-analysis [13].

Otherwise, different scenarios can result if no significant differences between IHT and placebo groups are found. In classical homeopathy, recovery requires the prescription of the individualized remedy at the adequate potency and dosage, so this is an important factor to be taken into consideration during the trial process because results may be biased. A negative result could be due to a mistaken election of the remedy and not because the IHT is inefficacious. Follow-up duration is also important. The selection of a suitable, individualized homeopathic medicine will not always be accomplished during six weeks of treatment, especially under double-blind conditions [21]. It has not been proved that six weeks of IHT is enough time to find a clinically relevant response in climacteric women with depression. In routine homeopathic consultation, a patient may require more than six weeks to recover from depression. However, for ethical reasons a longer follow-up is not possible because of the placebo group. Furthermore, homeopathic prescriptions may need to be modified depending on a patient’s individual response after homeopathic treatment is initiated. Once again, this could be problematic under double-blind conditions.

For ethical reasons women with severe depression will be excluded, so data of this trial will be able to prove an effective treatment in Mexican climacteric women with moderate to severe depression. Depression severity will be scored by the 17-item HRSD, which is a standardized instrument that has been used in many other clinical trials for depression. Another self-administered instrument, the BDI will also be used, so the results of the study might provide useful information in clarifying the controversy over the efficacy of homeopathy in depression. Use of these standardized instruments enables us to compare results with other trials published worldwide.

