The Hamilton Rating Scale of Depression (HRSD) and the Beck Depression Inventory (BDI) are two well-known standardized scales to assess depression severity used in trials worldwide. The Greene Climacteric Scale (GS) is also a standardized scale used in the Mexican population. It is intended specifically to be a brief and standard measure of core climacteric symptoms or complaints to be used for comparative and replicative purposes across different types of studies whether they are medical, psychological, sociological or epidemiological in nature. Three separate sub-scales measure vasomotor symptoms, somatic symptoms, psychological symptoms, and an additional probe is related to sexual function. Psychological symptoms can be further sub-divided to measure anxiety and depression [11,12].

Meta-analyses of antidepressant medications have reported only modest benefits over placebo treatment and, when unpublished trial data are included, the benefit falls below accepted criteria for clinical significance [13,14]. Specifically, a meta-analysis of clinical trial data submitted to the US Food and Drug Administration (FDA) revealed a mean drug-placebo difference in improvement scores of 1.8 points on the HRSD [15], whereas the National Institute for Clinical Excellence (NICE) used a drug-placebo difference of three points as a criterion for clinical significance when establishing guidelines for the treatment of depression in the UK. Antidepressants may be effective for severely depressed patients, but not for moderately depressed ones. Moreover, only about 50% of patients with MDD show a response (>50% reduction in baseline symptoms) and only about one in three attain remission (virtual absence of symptoms) within the first eight weeks of treatment [4,16-18].

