### Sample size calculation

Sample size calculation was estimated using G*Power (available at the University of Düsseldorf: http://www.psycho.uni-duesseldorf.de/abteilungen/aap/gpower3/). The sample size calculation is based on a previous study protocol for a randomized controlled trial of homeopathy for depression published by Adler *et al.*[21]. We assumed that *verum* treatment is better than placebo by 2.7 ± 6.0 (mean ± standard deviation) HRSD score points after six weeks [21], corresponding to an effect size = 0.45 (largest difference between any two groups to be detected/expected within group standard deviation = diff/de). To detect an effect size = 0.45, in a three-group design (1:1:1), using F-Test, with a 5% risk of type 1 error (α) and 83% power, 63 patients per group are required considering also a 10% drop-out rate.

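### The Discussion says the fluoxetine arm can show whether the drug-placebo difference is as small as in meta-analysis, but 57 to 63 women per arm cannot reliably separate 1.8 HRSD points from 0 or from 3

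*Protocol article*

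**What the plan says.** The Discussion first expects fluoxetine to differ significantly from placebo. It then notes that such differences have become harder to show, and gives the arm a second purpose: "a fluoxetine-arm will allow us to detect if in Mexican women in the climacteric stage with moderate to severe depression". What is to be detected, according to the rest of that sentence, is whether "the difference in HRSD score between fluoxetine and placebo is as small as it has been shown in some meta-analysis". No number, margin or precision is attached to it, and it cites reference 13.

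The Background supplies the numbers. It reports "a mean drug-placebo difference in improvement scores of 1.8 points on the HRSD" (reference 15) and says that the UK guideline body "used a drug-placebo difference of three points as a criterion for clinical significance".

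The Sample size calculation assumes an advantage for active treatment, which it puts as "better than placebo by 2.7 ± 6.0 (mean ± standard deviation) HRSD score points after six weeks". It converts this to a standardised effect of 0.45 and says that "with a 5% risk of type 1 error (α) and 83% power, 63 patients per group are required", a count that allows for 10% drop-out. The calculation is made "in a three-group design (1:1:1), using F-Test". Study design calls the trial a superiority trial. Statistical analysis names a one-way ANOVA followed by Bonferroni post-hoc comparisons. Fluoxetine versus placebo is part of the primary aim (Aims) and one of the three listed comparisons.

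**The concern.** The sentence states, without qualification, what the fluoxetine arm can do. To do it, the trial would need either good power at about the meta-analytic difference or an interval narrow enough to lie below the criterion for clinical significance. The sample size was set for a larger difference, 2.7 points, and the named tests look for superiority. A superiority test that fails to reach significance leaves open a zero, small or moderate effect.

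At stake is what may be concluded about the trial's active reference arm. If the stated capability is taken at face value, an imprecise estimate could pass as information about how small the antidepressant effect is in this population. The comparison of homeopathy with fluoxetine would then be read against it.

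**Working it through.** **Inputs.** SD 6.0, design difference 2.7, alpha 0.05 and 63 per arm including 10% drop-out (Sample size calculation). Evaluable per arm: 63 × 0.9 = 56.7, about 57. Small difference 1.8 and criterion 3 (Background). Three pairwise comparisons, so Bonferroni alpha = 0.05/3 (Statistical analysis). Pairwise tests are assumed two-sided because the article does not state sidedness. The pooled error has 3n − 3 degrees of freedom.

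**The plan's own figure.** The effect size is 2.7/6.0 = 0.45, as stated. For three groups, this range corresponds to Cohen's f between 0.45/√6 = 0.184 (third mean midway) and 0.45·√2/3 = 0.212 (two means equal). The noncentral F then gives power of 60% to 74% with 63 per arm and 56% to 69% with 57, so the stated 83% is not reproduced. That is a separate matter. The check below uses only n and the SD, and its result would stand even if 83% at 2.7 were right.

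**Precision.** SE = SD·√(2/n).
- n = 63: SE = 6.0 × √(2/63) = 1.07; 95% half-width = 1.973 × 1.069 = 2.11.
- n = 57: SE = 6.0 × √(2/57) = 1.12; 95% half-width = 1.974 × 1.124 = 2.22.
- Bonferroni half-widths: 2.416 × 1.069 = 2.58 and 2.418 × 1.124 = 2.72.

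An observed difference of exactly 1.8 would carry a 95% interval of about −0.3 to 3.9 (n = 63) or −0.4 to 4.0 (n = 57). Both contain 0 and 3.

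**If the true difference is 1.8** (noncentral t; joint coverage by simulation of 400,000 trials):

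| | 57 per arm | 63 per arm |
|---|---|---|
| Power against 0, alpha 0.05 | 36% | 39% |
| Power against 0, alpha 0.05/3 | 21% | 24% |
| 95% interval wholly below 3 | 18% | 20% |
| 95% interval includes 0 | 64% | 61% |
| 95% interval includes 3 | 81% | 80% |
| 95% interval includes both | 46% | 41% |

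For scale only: 80% power at 1.8 would need about 176 per arm unadjusted or 234 with Bonferroni, before drop-out.

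**Sensitivity to the SD.** The article does not say whether 6.0 is the SD of change or of final score. With 63 per arm and an assumed SD of 4 to 8, the half-width runs from 1.4 to 2.8 points, power for 1.8 against 0 from 71% to 24%, and power to separate 1.8 from 3 from 39% to 13%. For 80% power with 63 per arm, the SD would have to be about 3.6 (1.8 versus 0) or 2.4 (1.8 versus 3). Baseline adjustment, which the article does not mention, would reduce the SD to 6.0 × √(1 − 0.25) = 5.2 at an assumed correlation of 0.5. Power would then be 49% and 25%.

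**The case against.** **The target values are not in the sentence.** This stands as a limit. The Discussion cites reference 13, while the 1.8 is attached to reference 15 and the figure from reference 13 is not shown. The 3-point criterion also appears only in the Background. But 1.8 is the sole meta-analytic figure that the document offers. The Background also places references 13 and 14 below accepted clinical significance once unpublished data are counted. A claim that a difference is small needs some benchmark, and these are the document's own.

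**It is one sentence of rationale, not an aim or an analysis rule.** True. Rewording it changes no endpoint, test or sample size, and this limits the weight of the point. The comparison it describes is nevertheless part of the primary aim.

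**The trial could still succeed.** At a true 1.8 it would exclude zero in 36-39% of trials. A reader might infer that it cannot distinguish the values at all, but the figures support only that it cannot do so reliably.

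**A null result is not bound to occur.** A reader might infer that non-significance is the likeliest outcome anywhere between 1.8 and 3. It is not. Bonferroni power is about 50-55% at 2.7 and 60-65% at 3 (67-71% and 76-80% unadjusted). The statement holds at 1.8, not across the range.

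**Nothing shows an intent to misread a null result.** A reader might infer that non-significance will be reported as proof of a small effect. The article nowhere says so, and it expects a significant fluoxetine effect. How the result will be reported is conjecture and forms no part of this point.

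**Confidence intervals may be in a fuller plan.** Agreed. Their absence from a condensed article is not criticised here.

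**Conclusion.** The point holds as an overstated capability. At SD 6.0 and 57 to 63 women per arm, the fluoxetine-placebo difference will be known only to within about ±2.1 to 2.2 points, which exceeds both the 1.8-point distance to zero and the 1.2-point distance to the criterion (3 − 1.8). The named superiority tests cannot establish smallness by failing to reject.

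The conclusion rests on the stated SD and on 1.8 as the benchmark. An SD of 4 would bring power against zero to 71%, but power to separate 1.8 from 3 would still be only 39%. Even that favourable case does not deliver what the sentence promises. The point should be corrected, but it is not a flaw in the primary analysis.

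**What to change.** Replace the Discussion sentence with wording to this effect: *With about 63 women per arm, and assuming an SD of 6.0, the fluoxetine-placebo difference will be estimated to within about ±2.1 to 2.2 HRSD points (95% CI). The trial is not sized to detect or confirm a difference as small as 1.8 points, and a non-significant result will not be read as evidence that the difference is small or absent. Any statement about smallness will rest on the 95% CI read against 1.8 and 3 points.*

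It would also help to say in the same place which meta-analytic figure is meant, since the citation there differs from the one attached to 1.8 in the Background.

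The cost is a change of wording. No more patients are needed and no test changes. The drawback is that the stated capability of the fluoxetine arm becomes less favourable.
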